## Abstract

**Background:**

A number of studies, notably EPIC, have shown a descrease in colorectal cancer risk associated with increased fibre consumption. Whilst the underlying mechanisms are likely to be multifactorial, production of the short-chain fatty-acid butyrate fro butyratye is frequently cited as a major potential contributor to the effect. Butyrate inhibits histone deacetylases, which work on a wide range of proteins over and above histones. We therefore hypothesized that alterations in the acetylated proteome may be associated with a cancer risk phenotype in the colorectal mucosa, and that such alterations are candidate biomarkers for effectiveness of fibre interventions in cancer prevention.

**Methods an design:**

There are two principal arms to this study: (i) a cross-sectional study (FACT OBS) of 90 subjects recruited from gastroenterology clinics and; (ii) an intervention trial in 40 subjects with an 8 week high fibre intervention. In both studies the principal goal is to investigate a link between fibre intake, SCFA production and global protein acetylation. The primary measure is level of faecal butyrate, which it is hoped will be elevated by moving subjects to a high fibre diet. Fibre intakes will be estimated in the cross-sectional group using the EPIC Food Frequency Questionnaire. Subsidiary measures of the effect of butyrate on colon mucosal function and pre-cancerous phenotype will include measures of apoptosis, apoptotic regulators cell cycle and cell division.

**Discussion:**

This study will provide a new level of mechanistic data on alterations in the functional proteome in response to the colon microenvironment which may underwrite the observed cancer preventive effect of fibre. The study may yield novel candidate biomarkers of fibre fermentation and colon mucosal function.

**Trial Registration:**

Trial Registration Number: **ISRCTN90852168**

## Background

Since Burkitt's original observations on the inverse correlation between fibre (non-starch polysaccharides and resistant starch) intake and prevalence of colorectal cancer [1], a wide range of studies have addressed this relationship and the possible mechanisms by which fibre may protect against bowel cancer. Recent meta-analyses find a strong evidence base to support consumption of fibre-containing foods for prevention of several cancers [2], and the majority of studies in this area are supportive. There are exceptions, however, and two RCT studies, published in 2000, failed to demonstrate a protective effect [3,4]. These controversial findings have been the subject of several commentaries [5,6]. Potential explanations for this conflicting data include: differences between US and EU assays for fibre, different baseline levels of intake and the limitations of adenoma recurrence as a model for primary colorectal cancer prevention.

There are several mechanisms proposed for fibre's proposed cancer-preventive properties. These include dilution of luminal contents; reduction in transit time, which together will reduce exposure of the mucosa to luminal toxin; adsorbtion of bile acids; and production of protective short chain fatty acids (SCFAs: principally acetate, propionate and butyrate) through fermentation of fibre by endosymbiotic bacteria. Studies in rats treated with a colorectal carcinogen, have demonstrated a variable protective effect of different dietary fibre substrates and have linked this with changes in the luminal SCFA profile [7]. Gibson et al for example found that when rats consumed a diet with cellulose, a non-fermentable fibre, as principle fibre source, little protection from DMH-induced carcinogenesis was afforded. Oat-derived fibre, an acutely fermentable fibre which is rapidly turned over to SCFA in the caecum, but yields lower levels of SCFA in the distal colon and rectum, provided improved protection, but maximal protection was conferred by the more weakly fermentable wheat fibre, which yielded higher levels of SCFA in the distal colon and rectum. The study analysed SCFA levels in rats' stools on each regimen and found that the strongest correlation with cancer prevention in this model occurred on diets which gave maximal elevation of faecal butyrate. Not surprisingly this data has led to a resurgence of interest in the actions of butyrate.

Roediger [8] was first to show that butyrate is the preferred metabolite of colon epithelial cells. In his studies, primary epithelial cells from rat colon were incubated with labelled glucose and labelled butyrate. Butyrate was found to be metabolised in preference to glucose, which is available to colonocyte in vivo through the vasculature. The use of butyrate as an energy souce is inefficient (by comparison with glucose) and it has been suggested that this represents an evolutionary adaptation to recover the maximum energy available from the high-fibre diets consumed by our paleolithic ancestors.

The effect of butyrate on cells grown in vitro is to drive both cell cycle arrest and apoptosis. Both of these alterations in cell fate occur at concentrations of butyrate readily achieved in the colon lumen through fibre fermentation. Cell cycle arrest has variously been reported as G1 arrest, G2 arrest and mitotic bypass [9-11]. Several reports have shown that the apoptosis triggered by butyrate in vitro is associated with dysregulation of Bcl2 family proteins especially upregulation of BAK and downregulation of BclxL [12-14], rather than cellular damage.

These in vitro data contrast with studies on the in vivo or ex vivo effects of butyrate. Takayama's studies investigating the effect of increasing fibre intake after restriction, using a variety of animal models, have shown that switching to a high fibre diet is associated with an increase in colon crypt length, cellularity and proliferation [15-17]. Hass [18] used ex vivo guinea pig colon mucosa in an Ussing chamber model and monitored rates of cell death. When tissue was maintained in an osmotically balanced chamber, widespread cell death was found on the epithelium and this was associated with up-regulation of Bax. When butyrate was added to the chamber, however, there was reduced cell death and no Bax upregulation. Furthermore, studies of diversion colitis show that widespread cell death occurs after diversion of the faecal stream and loss of luminal content [19]. This condition may be ameliorated by butyrate enema [20].

Recent studies have shown that elevation of luminal SCFA causes no direct increase in levels of epithelial apoptosis [21,22], but causes a significant increase in the level of apoptosis after a genotoxic challenge. These in vivo data are suggestive of a model whereby butyrate's antineoplastic action is not in the induction of apoptosis per se, but through sensitization of cells to damage. The observations made in vitro that butyrate elevated levels of pro-apoptotic Bcl2 family proteins, and downregulated their anti-apoptotic counterparts could be predicted to sensitize cells in precisely this way and we have recently proposed this as a model [15].

How might butyrate alter cell functionality in this way? Although recognised as a metabolite, butyrate is also a potent inhibitor of histone deacetylases (HDACs) - [23]. HDACs are primarily recognised as one part of the regulatory mechanism for governing histone acetylation levels in concert with their agonist enzymes the histone acetyl transferases (HATs). The acetylation state of histones is thought to be a potent governor of gene transcription at both a specific and regional level of the chromatin. A number of publications have shown widespread alteration in gene expression after treatment of cells in vitro with butyrate, indicating as much as 10% of genes may be affected by butyrate either directly or indirectly. However more recently several groups have identified other acetyl proteins in the nucleus and cytosol, and HDAC activities have been found in both cellular compartments [24,25]. Amongst the acetyl proteins identified are nuclear structural proteins, transcription factors including p53, Sp1, Sp3 [26] and structural proteins including tubulin and cytokeratins [27,28]. Our own preliminary findings using pan-specific antiacetyl lysine antibodies indicate tens or hundreds of acetyl proteins in cell lines ([name] & [name], unpublished). Acetylation has been proposed as being as important as phosphorylation in the regulation of protein function [29]. This is reinforced by the observation that HATs and HDACs are frequently mutated in cancer, which may lead to an alteration in the acetylation landscape of the cell permissive for cancer progression.

Taken together these data allow us to generate an hypothesis that i) colorectal carcinogenesis will be associated with an alteration in global protein acetylation, ii) reduced levels of butyrate will cause alterations in global protein acetylation, which may also be permissive for colorectal cancer progression, iii) that elevation of fibre levels and consequent butyrate levels may reduce or reverse these processes and restore a "normal" profile of protein acetylation.

## Methodsand design

### Overall Aim of the study

To determine if there is a link between global protein acetylation, fibre intake and fermentation, and colorectal carcinogenesis.

#### Primary Aims

1. To undertake a cross-sectional study of global protein acetylation profiles in normal subjects and those with colonic polyps and colorectal cancer. This study arm is named FACT OBS.

2. To determine, in the same clinical groups, the relationship between global protein acetylation profile and faecal SCFA levels.

3. To undertake a fibre supplementation study in morphologically normal GI patients and patients with colonic polyps to determine the effect of fibre supplementation on the global acetylation profile. This study arm is named FACT INT.

#### Secondary Aims

1. To investigate in the above groups whether there is an alteration in crypt proliferation index in response to carcinogenesis and to fibre.

2. To investigate in the above groups whether there is an alteration in the apoptotic index in response to carcinogenesis and to fibre.

3. To investigate in the above groups whether this is an alteration in expression of key apoptotic regulators in response to carcinogenesis and to fibre.

4. To establish the effect of bowel cleansing preparations on the parameters measured under the secondary aims. This study arm is named FACT VAL.

5. Evaluation of the EPIC Food Frequency Questionnaire as a proxy measure of faecal SCFA.

#### Ethics

Ethics committee approval was obtained from the North Sheffield Research Ethics Committee prior to recruiting (Reference number: 06/Q2308/93)

#### Patient Recruitment and sample collection

##### FACT OBS recruitment

Recruitment targets were 30 normal, 30 polyp and 30 cancer patients. Patients were primarily recruited via outpatient clinics and through patient databases at Sheffield's Northern General Hospital and Royal Hallamshire Hospital. All patients were attending for diagnostic colonoscopy and patient and researchers were unaware of the diagnosis at time of recruitment and consent. Up to 10 biopsies were collected at endoscopy from these patients. Biopsies were collected with a Radial Jaw 4 2.8 mm forceps (see table 1). Two weeks post-endoscopy, patients were asked to provide a stool sample and completed a Food Frequency Questionnaire (FFQ).

**Table 1 T1:** Position and uses of biopsies taken during endoscopy for the FACT OBS and FACT INT arms of this study.

Site	Biopsies	Purpose
**FACT OBS**		

Mid-sigmoid	1	Whole mount
	2	Immunohistochemistry
	3	Proteomics
	4	Proteomics

Contralateral	1	Immunohistochemistry
	2	Proteomics
	3	Proteomics

Lesion	1	Immunohistochemistry
	2	Proteomics
	3	Proteomics

**FACT INT**		

Mid-sigmoid	1	Whole mount
	2	Immunohistochemistry
	3	Immunohistochemistry
	4	Proteomics
	5	Proteomics
	6	Proteomics
	7	Proteomics
	8	Proteomics
	9	Proteomics
	10	Proteomics

##### FACT VAL recruitment

Recruitment of patients to the FACT VAL arm of the study was from the same routes as for the FACT OBS arm. Patients indicating a willingness to return for a repeat flexible sigmoidoscopy without bowel preparation were recruited specifically to this arm of the study. The recruitment target for this arm was 6 patients with a first procedure following preparation with Kleanprep and 6 patients with a first procedure following preparation with Picolax.

##### FACT INT recruitment

Recruitment target for the FACT INT study is 20 normal and 20 polyp subjects consuming an habitually low fibre diet. Patients will be recruited via the outpatients clinics for the bowel screening programme, Northern General Hospital, Sheffield. The biopsy protocol is summarised in Table 1. Stool samples, FFQ and a four day food diary will be collected circa 2 weeks after the endoscopy. Subjects will be asked to comply with a high fibre diet for an eight week period (including a 2 week ramp phase). Stool sampling and a further food diary will be collected at the end of the 8 week intervention, patients will then return for a second endoscopy with the same biopsying protocol.

##### Power calculation and sample size

There are no previous studies investigating addressing alteration in global protein acetylation *in vivo *and therefore no data upon which to base a power calculation.

#### Inclusion and Exclusion Criteria

##### Inclusion criteria

Male subjects (FACT OBS only), Aged > 40, Low habitual NSP and RS consumption (FACT INT only), Low level of faecal butyrate BMI 20-29.

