##### Exclusion criteria

Female (FACT OBS only), Cancer (FACT INT only), Habitual consumers of a diet high in NSP and RS, Smokers, Type 2 diabetics, Dieters, Inflammatory Bowel Disease.

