#### Primary outcome measure

##### Development of a methodology for studying global protein acetylation in biopsy samples and proof of principle studies

It is the goal of this study to link alterations in global proteins acetylation in the colon mucosa to levels of butyrate, the most potent HDACi produced though colonic fermentation of fibre. In order to determine levels of butyrate and other SCFA, the stool sample collected from patients will be weighed and extracted freshly (within 3 hr of production) using a standard procedure [29] to yield SCFA. The absolute level of levels of each SCFA will be determined by gas chromatography ion collaboration with [name], University of Newcastle upon Tyne. The acetylated proteome will be analysed by a method reported elsewhere ([name] et al., in preparation), modified from a published protocol for analysis of global protein acetylatyion [30]. In brief, tissue samples will be lysed, soluble protein extracted and acetyl proteins immunoprecipitated before separation by 2d gel electrophoresis. Owing to the numbers of biopsies' worth of immunoprecipitate required for a 2d gel (6-8 biopsies), a pooling strategy will be required for the FACT OBS analysis. Patients will be pooled into deciles within pathology groups (i.e. deciles within adenoma group, cancer group, normal group) according to faecal butyrate levels, and all biopsies in each pool will be used for a single 2d gel.

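### As labelled, the low-butyrate inclusion and the high-fibre exclusion also apply to FACT OBS, and narrow the exposure range that arm is meant to study

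*Protocol article*

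**What the plan says.** One pair of eligibility lists in the Protocol article serves the study arms, with arm-specific items labelled in brackets.

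- **Inclusion criteria:** the male-sex item is limited to FACT OBS. The list then reads "Low habitual NSP and RS consumption (FACT INT only), Low level of faecal butyrate BMI 20-29". The fibre item carries a label. The butyrate item has no label, no threshold and no separator before the BMI range.
- **Exclusion criteria:** "Female (FACT OBS only), Cancer (FACT INT only), Habitual consumers of a diet high in NSP and RS, Smokers". The sex and cancer items are labelled; the item on high intake of non-starch polysaccharides (NSP) and resistant starch (RS) is not.

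FACT OBS is given these tasks:

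- Abstract, Methods and design: "In both studies the principal goal is to investigate a link between fibre intake, SCFA production and global protein acetylation".
- Primary Aims, item 2: to determine, in the cross-sectional groups, "the relationship between global protein acetylation profile and faecal SCFA levels".
- Secondary Aims, item 5: "Evaluation of the EPIC Food Frequency Questionnaire as a proxy measure of faecal SCFA".
- Primary outcome measure: "Patients will be pooled into deciles within pathology groups", ranked by faecal butyrate, with one gel per pool.
- Secondary outcome measures: proliferation and apoptosis are to be related to fibre intake, SCFA and butyrate in FACT OBS samples.

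On size and timing, FACT OBS recruitment states "Recruitment targets were 30 normal, 30 polyp and 30 cancer patients" and "Two weeks post-endoscopy, patients were asked to provide a stool sample and completed a Food Frequency Questionnaire (FFQ".

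**The concern.** Items that plainly hold throughout, such as age, BMI and smoking, carry no label, while items meant for one arm do. A reader following that convention must apply the low-butyrate inclusion and the high-fibre exclusion to FACT OBS.

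That arm is observational, and its information about fibre and SCFA comes from how much patients differ on them. Both criteria cut from the top. Deciles can still be formed, but the highest one then holds the least low patients rather than patients with high butyrate. In the questionnaire evaluation, both variables would be restricted. What is at stake is the ability of FACT OBS to detect the associations it was set up to find, and clarity about which patients belong in its analysis.

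**Working it through.** **Labels side by side**

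| Item | Label | Applies to FACT OBS as written? |
|---|---|---|
| Male sex (inclusion), female sex (exclusion) | FACT OBS only | Yes |
| Low NSP/RS intake (inclusion) | FACT INT only | No |
| Cancer (exclusion) | FACT INT only | No |
| Low faecal butyrate (inclusion) | none | Yes |
| High NSP/RS intake (exclusion) | none | Yes |

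The recruitment text describes a habitually low-fibre population for FACT INT and sets no such limit for FACT OBS.

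**Timing.** FACT OBS patients consent, undergo endoscopy with biopsy, and give stool two weeks later. A butyrate criterion can therefore only remove patients after biopsy, or go unapplied.

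**Structure of the gel analysis.** 30 + 30 + 30 = 90 patients; 30 per group / 10 deciles = 3 patients per gel, so 10 gels per group and 30 in all.

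**Illustration of the loss (patient-level measures only).** The protocol has no power calculation, effect size or cut-off to reproduce. Assumed: bivariate normality, true r = 0.40, two-sided alpha 0.05, and admission of only the lowest fraction q of the butyrate distribution.

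- SD ratio after truncation: u = sqrt(1 − bλ − λ²), where b = Φ⁻¹(q) and λ = φ(b)/q.
- Restricted correlation: r' = r·u / sqrt(1 − r² + r²u²).
- Power by Fisher z: Φ(atanh(r')·sqrt(n − 3) − 1.960).

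Worked case, q = 0.50: b = 0, λ = 0.3989/0.5 = 0.798, u = sqrt(1 − 0.637) = 0.603. Then r' = 0.241 / sqrt(0.84 + 0.058) = 0.254. At n = 90: atanh(0.254) × sqrt(87) − 1.960 ≈ 0.47, giving power 0.68.

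| Admitted | u | r' | Power, n=90 | Power, n=30 |
|---|---|---|---|---|
| All | 1 | 0.400 | 0.98 | 0.60 |
| Lowest 90% | 0.844 | 0.346 | 0.92 | 0.47 |
| Lowest 75% | 0.731 | 0.304 | 0.83 | 0.37 |
| Lowest 50% | 0.603 | 0.254 | 0.68 | 0.27 |
| Lowest 33% | 0.529 | 0.225 | 0.57 | 0.22 |

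The n=30 column is one pathology group. At n=90, over the same cuts, an assumed r of 0.30 takes power from 0.82 to between 0.69 and 0.34; an r of 0.50 takes it from above 0.99 to between 0.99 and 0.80.

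**The case against.** The strongest reply is that the missing labels are a slip. The butyrate item runs straight into the BMI range, which suggests garbled text; the stool timing makes it unworkable at FACT OBS entry; and the pooling plan mentions no butyrate ceiling. This stands as far as it goes: the text shows what is prescribed, not what was done. A reader might infer that FACT OBS was in fact truncated, but the protocol reports no such exclusions.

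Other stronger readings also go further than the document:

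- **That the two lists flatly contradict each other on fibre.** They do not. Requiring low intake in FACT INT and excluding high intake everywhere are compatible; FACT OBS would then admit low and middle intakes. The exclusion could be deliberate.
- **That both criteria could act only after biopsy.** This is firm for butyrate alone. Habitual diet can be asked about at recruitment, and the questionnaire is not named as the screening tool.
- **That the associations are biased.** Selection on the exposure lowers correlation and precision, but under a linear model it does not bias the slope on that exposure.
- **That a comparison of butyrate between pathology groups is distorted.** No stated aim makes that comparison. Primary Aim 1 compares acetylation profiles and is less directly affected.
- **That the power figures describe the acetylation analysis.** They do not. That analysis rests on pooled gels, and the figures fit only measures taken on individual patients.

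**Conclusion.** The point holds as a defect in how the criteria are assigned to arms. Read by the lists' own convention, two exposure-based criteria govern FACT OBS and narrow the fibre and butyrate range on which one primary aim, one secondary aim, the decile contrast and the proliferation and apoptosis analyses depend. One of the two cannot be applied at entry to that arm.

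The direction of the effect is clear: weaker correlations, less precision and a smaller decile contrast. Its size is unknown, because no cut-off is stated. At an assumed r of 0.40, the illustration runs from a modest loss (0.98 to 0.92, lowest 90% admitted) to a serious one (0.98 to 0.57, lowest third admitted) for patient-level measures at n=90. Whether any FACT OBS patient was excluded on these grounds cannot be told from the document. If the omission is a slip, it is easily corrected; if it is intended, it works against a primary aim.

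**What to change.** Label the low-butyrate inclusion and the high NSP/RS exclusion as FACT INT only. Add one sentence stating that FACT OBS recruits and analyses patients across the full range of fibre intake and faecal butyrate, and that any FACT OBS patient with samples who would otherwise be dropped on these grounds stays in the analysis.

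If the high-fibre exclusion in FACT OBS is deliberate, say so and limit that arm's conclusions to low and middle intakes.

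The cost is two labels and a sentence. The drawback is that the high NSP/RS exclusion, once limited to FACT INT, largely duplicates that arm's low-intake inclusion. The label also does not settle when butyrate is measured for FACT INT eligibility, since stool there too is collected about two weeks after the first endoscopy. FACT OBS recruitment is described in the past tense, so the practical effect may fall mainly on who is analysed.

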#### High Fibre intervention

The primary goal of the intervention arm is to elevate colonic SCFA levels, which will be monitored through analysis of faecal SCFA. Elevation of fermentable fibre intake is a rapid and amenable mechanism to achieve this goal. Patients recruited to the FACT INT arm will be offered a range of high-fibre foods, including switch to wholemeal bread, fruit, dried fruit snacks, from a basket of options identified by the research team (Additional File 1). Foods will be ordered by the researcher and delivered by a supermarket home delivery to the patients' homes. Compliance will be estimated and supported through interim telephone calls and 24 hr recall estimates.

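### FACT INT selects on low faecal butyrate, then looks for a rise in it with one described pre-diet stool collection and no control group, so regression to the mean can pass for a fibre effect

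*Protocol article*

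**What the plan says.** **Entry.** The protocol article, under Inclusion criteria, lists "Low level of faecal butyrate BMI 20-29". There is no cut-off and no arm tag. Other entries in the same list are tagged, for example "Low habitual NSP and RS consumption (FACT INT only", so an untagged entry applies to FACT INT as well as FACT OBS.

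**Outcome.** The abstract states: "The primary measure is level of faecal butyrate, which it is hoped will be elevated by moving subjects to a high fibre diet". The section High Fibre intervention adds: "The primary goal of the intervention arm is to elevate colonic SCFA levels, which will be monitored through analysis of faecal SCFA".

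**Stool collection.** Under FACT INT recruitment there is one occasion before the diet, "Stool samples, FFQ and a four day food diary will be collected circa 2 weeks after the endoscopy", and one after it, "Stool sampling and a further food diary will be collected at the end of the 8 week intervention". No screening stool or repeat baseline is described.

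**Comparator.** The abstract calls this arm "an intervention trial in 40 subjects with an 8 week high fibre intervention", and the recruitment section states: "Recruitment target for the FACT INT study is 20 normal and 20 polyp subjects consuming an habitually low fibre diet". Both pathology groups receive the diet. No untreated group is described.

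**The concern.** A stool butyrate value contains a stable personal level and a transient part: day-to-day variation, sampling and assay error. People admitted because a single value was low have, on average, a transient part below zero at that moment. On re-measurement it returns to an average of zero and the group mean rises, whatever the diet does. The rise is in the direction the study hopes to see.

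A concurrent control group selected in the same way would show the same rise and allow it to be subtracted. FACT INT has none. The normal and polyp groups cannot stand in for one, because both are selected and treated alike. Nor can analysis correct for it from data the article describes. That would need the within-person correlation of untreated repeat stools. FACT OBS collects one stool per patient, and no stool collection is described for FACT VAL.

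At stake is the statement that the diet raised faecal butyrate, on which the rest of the intervention arm's argument builds.

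**Working it through.** The article has no figure to reproduce: the section Power calculation and sample size says that no data exist to support one.

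**Inputs from the article:** selection on low butyrate; one pre-diet and one post-diet stool occasion; n = 40 (20 normal + 20 polyp), all treated.

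**Assumptions, not in the article:** values are normal and exchangeable; a share q of candidates counts as low; two stool measurements in one person correlate at r; the qualifying value is also the baseline; the diet has no effect; change is tested with a pooled paired t-test at two-sided 5%, so a false increase should occur in 2.5% of trials.

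**Step 1, expected spurious rise** in between-person SD units, with φ the standard normal density and z_q the normal quantile at q:

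rise = (1 − r) × φ(z_q) / q

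- q = 0.75, r = 0.9: 0.1 × 0.3178 / 0.75 = 0.04 SD
- q = 0.50, r = 0.5: 0.5 × 0.3989 / 0.50 = 0.40 SD
- q = 0.25, r = 0.5: 0.5 × 0.3178 / 0.25 = 0.64 SD

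**Step 2, chance of a significant increase.** For q = 0.5 and r = 0.5, the variance of baseline among those selected is 1 − 2/π = 0.363. The variance of change is (1 − r)² × 0.363 + (1 − r²) = 0.091 + 0.750 = 0.841, SD 0.917. The expected t value is about 0.399 / 0.917 × √40 = 2.75, against a critical value of 2.02. Simulation (20,000 or more trials per setting) gives:

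| Share eligible | r | Spurious rise (SD) | False increases, n = 40 |
|---|---|---|---|
| Lowest 75% | 0.9 | 0.04 | 9% |
| Lowest 75% | 0.7 | 0.13 | 18% |
| Lowest 75% | 0.5 | 0.21 | 28% |
| Lowest half | 0.9 | 0.08 | 20% |
| Lowest half | 0.7 | 0.24 | 52% |
| Lowest half | 0.5 | 0.40 | 76–77% |
| Lowest half | 0.3 | 0.56 | 91% |
| Lowest quarter | 0.9 | 0.13 | 43% |
| Lowest quarter | 0.5 | 0.64 | 99% |

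Without selection the rate is 2.2% to 2.6%, so the excess comes from the selection.

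**Step 3, sensitivity to the analysis.** If the two pathology groups are tested separately (n = 20 each), the middle case (lowest half, r = 0.5) has expected t = 0.399 / 0.917 × √20 = 1.95 and a false-increase rate of about 45% per group. The spurious rise itself is unchanged.

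**Step 4, remedies under the same model.** Measuring change from a second pre-diet stool that played no part in eligibility gives a mean change of 0.00 SD and false increases of 2.3% to 2.8%. A concurrent control selected the same way (20 v 20) gives 2.4% to 2.7%.

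**The case against.** **The qualifying stool may not be the baseline stool.** The article never says that the collection two weeks after endoscopy decides eligibility. By then the subject has been recruited and Table 1 has ten biopsies taken, an odd moment for an entry test. A screening stool may exist in the full protocol, or the criterion may not have been applied as a gate. This stands as a limit: a reader might infer that the article states the double use, and it does not. But it describes no other pre-diet collection, so a butyrate criterion applied as written leaves no other value to use. The plural in the collection sentence does not settle the matter: averaging several samples shrinks the bias but does not remove it if the same average decides entry.

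**The criterion is unclear.** It runs into the BMI condition without a separator, and it fits FACT OBS poorly, because patients there are ranked into deciles of butyrate. The FACT INT recruitment section mentions only low fibre intake. All true, but the criterion is in the list and nothing exempts FACT INT.

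**The bias may be small.** With candidates already chosen for low fibre intake, the butyrate condition might exclude few; with stable stool values, regression is slight. This stands. A reader might take 77% as the trial's error rate, but the documents supply neither quantity behind it, nor the pooled test.

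**Acetylation is not selected on.** The section Primary outcome measure and the third primary aim concern acetylation. A reader might infer that any acetylation finding, or any link between acetylation and butyrate, is undermined. The documents do not support that. Acetylation change is biased only so far as it follows the transient part of butyrate, and noise in butyrate change would tend to weaken an association rather than create one.

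**Conclusion.** The concern holds in conditional form. The article makes low faecal butyrate an entry condition for an uncontrolled arm whose stated goal is to raise it, and describes one pre-diet collection. If that collection both qualifies the subject and sets the baseline, the change in butyrate is biased upward, and the data the article describes cannot separate that from a diet effect.

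The direction is certain under this reading; the size is not. It ranges from minor to severe, as tabulated, and vanishes only if stool butyrate is perfectly repeatable or the criterion excludes nobody. A separate screening stool in the full protocol would remove the selection bias. The direct effect is on the faecal butyrate and SCFA change.

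**What to change.** **Preferred:** remove low faecal butyrate as an entry criterion for FACT INT and select on low habitual NSP and RS intake, which is already a criterion. Cost: a change of eligibility wording and a less enriched sample.

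**If the criterion is kept:** state its cut-off, qualify on one stool, take the baseline from a separate later stool collected before the diet starts, and exclude the qualifying value from the change analysis. Cost: one extra stool per subject. It must be planned in advance, since a pre-diet sample cannot be obtained afterwards.

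If the full protocol already has a separate screening stool, saying so and naming the baseline stool is enough for this point.

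Either change removes the selection bias only. Without a control group, time trends and any recovery after bowel preparation stay mixed with the diet effect, and the study's conclusions should say so.
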